#### Secondary outcome measures: Participant perceptions of the program

Qualitative responses about the training programs are gathered from participants to assess the suitability of the programs for older adults.

##### Program feedback form

This includes specific questions inviting participants to appraise the *Fit Bodies, Fine Minds *program. Written responses are invited on issues such as positive and negative outcomes of participation in the program, barriers to and facilitators of participation, enjoyment of activities and setting, and suitability of duration and frequency of sessions.

The form also includes two questions with 5-point Likert-scale response options. The first question is *How enjoyable was Fit Bodies, Fine Minds? *The response options are *extremely enjoyable*, *very enjoyable*, *quite enjoyable*, *somewhat enjoyable*, and *not at all enjoyable*. The second question is *How did you feel about attending Fit Bodies, Fine Minds? *The response options are *I looked forward to it ALL of the time*, *I looked forward to it MOST of the time*, *I looked forward to it SOME of the time*, *I could take it or leave it*, and *I DID NOT look forward to it at all*.

### Analyses

Analysis of variance techniques will be used to assess changes over time (baseline, post-test, follow-up), and differences between groups, on the measures of aerobic capacity and cognitive functioning. Mean scores and variability scores will be used in these analyses. Variability scores may provide a more sensitive indicator than mean scores, of changes in cognitive functioning in older adults [71]. Where appropriate age, education and gender will be included as covariates. The Reliable Change Index will be used to determine the percentage of participants who demonstrate a significant change in performance, relative to their individual baseline [72,73]. This approach may provide a more accurate picture of changes experienced by participants than simple group differences [72,73]. Regression techniques will be used to identify the influence of changes in aerobic capacity on cognitive functioning. Regressions techniques will also be used to identify the influence of changes in psychological wellbeing on cognitive functioning.

The qualitative data will be analysed to identify themes related to participant perceptions of the program.

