### Sample size

Ninety-nine participants will be recruited for the study. A sample size of 12 participants in each of the three groups would enable detection of a within-group difference, from baseline to post-test, of 1 item (SD = 1.1) on Digit Span and 184 milliseconds (SD = 198) on Choice Reaction Time. Twenty participants in each group would enable detection of a between-group difference, at post-test, of 2 items (SD = 2.2) on Digit Span. Twenty-nine participants in each group would enable detection of a between-group difference, at post-test, of 118.8 milliseconds (SD = 160) on Choice Reaction Time. These sample size calculations assume a two-tailed alpha level of 0.05 and a power of 80%. The effect sizes and standard deviations are based on results from previous studies of physical activity for cognitive functioning in older adults (e.g. [11,49]). To account for attrition over time, the required sample size (29) is increased by 10% to 33 participants per group.

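### Choice Reaction Time is sized on post-test values alone, but the planned ANOVA reads as a change analysis without the baseline score as covariate; baseline-adjusted ANCOVA would protect the stated power at no cost

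*Protocol article*

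**What the plan says.** The Sample size section of the protocol article gives two kinds of calculation for Choice Reaction Time, both at two-sided 5% and 80% power.

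- Within group, 12 participants per group, for a baseline to post-test difference of "184 milliseconds (SD = 198) on Choice Reaction Time".
- Between groups: "Twenty-nine participants in each group would enable detection of a between-group difference, at post-test, of 118.8 milliseconds (SD = 160) on Choice Reaction Time". This is the largest of the stated requirements. It is the one inflated by 10% to 33 per group, so it sets the trial's size.

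For Digit Span the same section gives 12 per group for "detection of a within-group difference, from baseline to post-test, of 1 item (SD = 1.1) on Digit Span", and then: "Twenty participants in each group would enable detection of a between-group difference, at post-test, of 2 items (SD = 2.2) on Digit Span".

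The Analyses section describes the comparison as follows: "Analysis of variance techniques will be used to assess changes over time (baseline, post-test, follow-up), and differences between groups". On adjustment it adds: "Where appropriate age, education and gender will be included as covariates". A measure's own baseline score is not on that list. The first hypothesis in the Discussion is that both training groups improve relative to control, which is a between-group difference in change. The Measurements section has every measure except the qualitative feedback taken at baseline, post-test and follow-up.

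**The concern.** The power statement and the analysis appear to concern different contrasts. The 29 per group is for post-test values compared once, with no use of baseline. An ANOVA in which baseline is one level of time estimates the treatment effect as a difference in change. The precision of that contrast depends on the SD of change, not on the post-test SD.

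The two SDs are related through the pre-post correlation. When the correlation is below 0.5, subtracting baseline adds more noise than it removes, and a change analysis is weaker than one that ignores baseline. The protocol's own change SD (198) exceeds its post-test SD (160), which is that situation. At stake is whether the comparison that fixes the trial's size has the power promised for it.

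**Working it through.** **Inputs (Sample size section).** Between-group difference 118.8 ms, post-test SD 160 ms, 29 per group; within-group change 184 ms, SD 198 ms, 12 per group; two-sided 5%, 80% power.

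**1. Reproduce the 29.** n = 2(1.960 + 0.842)² × (160/118.8)² = 15.70 × 1.814 = 28.5, so 29. By the t distribution, power at 29 is 79.3%. The stated figure is a two-sample comparison of post-test values.

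**2. What kind of SD is 198?** A paired t test with 184/198 = 0.929 needs 11.2 participants, so 12, with 83.4% power at 12. Read as an independent-sample SD, the same ratio would need about 20 per group. The stated 12 therefore fits only if 198 is used as the SD of the baseline to post-test difference. Digit Span behaves alike: 1/1.1 paired needs 11.6, so 12; as independent samples, 20.

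**3. Power for a difference in change, using 198.** Under randomization the expected difference in change equals the expected post-test difference, so 118.8 ms carries over. The standardized effect is 118.8/198 = 0.60.

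- Power at 29 per group: 61.2% (61.7% with error pooled over three groups, 84 df).
- Power at 33 per group with nobody lost: 67.0%.
- Needed for 80%: 15.70 × (198/118.8)² = 43.6, so 44 by the normal formula and 45 by t.
- Three-group F test on change, both training groups benefiting by 118.8 ms: 63.6%.

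**4. Implied correlation.** Assuming SD 160 at both visits, 198² = 2 × 160² × (1 − ρ), so ρ = 1 − 39,204/51,200 = 0.234.

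**5. Dependence on ρ, and comparison with ANCOVA.** With SD 160 at both visits, the change SD is 160√(2(1 − ρ)) and the ANCOVA residual SD is 160√(1 − ρ²). Power is at 29 per group by two-sample t, ignoring the one degree of freedom spent on the covariate.

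| ρ | Change SD | Power, change | ANCOVA SD | Power, ANCOVA |
|---|---|---|---|---|
| 0 | 226.3 | 50.2% | 160.0 | 79.3% |
| 0.234 | 198.0 | 61.2% | 155.5 | 81.5% |
| 0.3 | 189.3 | 65.1% | 152.6 | 83.0% |
| 0.5 | 160.0 | 79.3% | 138.6 | 89.4% |
| 0.6 | 143.1 | 87.4% | 128.0 | 93.5% |
| 0.7 | 123.9 | 94.8% | 114.3 | 97.3% |

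The ordering is algebraic. The factor 1 − ρ² = (1 − ρ)(1 + ρ) never exceeds 1 (post-test only) or 2(1 − ρ) (change).

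**6. Digit Span.** The same derivation gives ρ = 1 − 1.1²/(2 × 2.2²) = 1 − 1.21/9.68 = 0.875. A change analysis of 2 items with SD 1.1 at 20 per group has over 99.9% power, against 80.0% for post-test values. Here the change analysis gains.

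**The case against.** A reader might infer that the design fails to deliver 80% power under its stated analysis. The article does not support so firm a statement, for three reasons.

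- **The model is inferred.** The Analyses section names neither a repeated-measures model nor a group-by-time test. Its wording is broad enough to cover an ANCOVA at post-test, the sized contrast is explicitly at post-test, and an article may leave the exact model to a fuller plan. This stands, so the change analysis is the most natural reading and not an established fact. The stated covariate list does, however, leave out the baseline score.
- **The 61% is conditional.** The SDs come from more than one earlier study, so 198 and 160 may belong to different samples and tasks, and this trial's task was built for it. The implied correlation also assumes equal SDs at the two visits. With a baseline SD of 130 it would be 0.08, with 200 it would be 0.41 and with 240 it would be 0.57. This stands: by a correlation of about 0.5 the shortfall is gone.
- **It concerns one outcome.** Digit Span goes the other way, subject to the same caution about pairing SDs. This also stands, although Choice Reaction Time is the comparison that sets the trial's size.

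A reader might also infer that anyone who misses the 40-week visit would be dropped from the 16-week comparison. That holds for a classical complete-case repeated-measures ANOVA, but the article does not say how missing visits are handled.

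Finally, a change analysis is valid under randomization, since it estimates the same effect. The issue is precision only.

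**Conclusion.** The point holds in a limited form. The between-group sample size for Choice Reaction Time was computed for post-test values alone and does not match a change-based analysis. If the protocol's change SD of 198 ms applies together with the 118.8 ms difference, power at 29 per group could be as low as about 61%. If the pre-post correlation is 0.5 or more with SD 160 at both visits, a change analysis has about 79% or better. The documents do not settle which case applies, and they show no general shortfall across outcomes.

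The recommendation does not depend on settling it. At every correlation examined, baseline-adjusted ANCOVA has more power than the change analysis, and it is never materially below the post-test-only comparison on which the 29 rests. This is a free improvement in precision; no bias is shown.

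**What to change.** In the Analyses section, name as the between-group analysis an ANCOVA of the 16-week score on arm, with that measure's baseline score always included as a covariate alongside age, education and gender where these are used. Treat the 40-week score in the same way, with baseline as a covariate and not as a level of time. In the Sample size section, restate the power for that analysis: at 29 per group about 79% at zero correlation, 82% at the 0.23 implied by the protocol's own SDs, and 97% at 0.7, with the assumed correlation given.

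The cost is wording only. Baseline is already measured for every outcome concerned, and the sample size, visits and procedures do not change.

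### The group comparison is sized on a post-test difference but the analysis is framed on change without the baseline score as covariate; if groups are tested on change, Choice Reaction Time power may be about 61%, against about 82% with baseline adjustment

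*Protocol article*

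**What the plan says.** The Sample size section of the protocol article fixes the recruitment target with this calculation: "Twenty-nine participants in each group would enable detection of a between-group difference, at post-test, of 118.8 milliseconds (SD = 160) on Choice Reaction Time". It uses two-sided alpha 0.05 and 80% power, and 29 is then raised to 33 for attrition. The same section gives a within-group calculation for 12 participants per group, for a baseline-to-post-test difference of "1 item (SD = 1.1) on Digit Span and 184 milliseconds (SD = 198) on Choice Reaction Time". A third calculation reads "Twenty participants in each group would enable detection of a between-group difference, at post-test, of 2 items (SD = 2.2) on Digit Span". The effects and SDs are attributed to earlier studies, in the plural.

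The Analyses section describes the comparison differently: "Analysis of variance techniques will be used to assess changes over time (baseline, post-test, follow-up), and differences between groups". On adjustment it says "Where appropriate age, education and gender will be included as covariates". The baseline score of the test being analysed is not named, although the Measurements section has all quantitative outcomes measured at baseline, post-test and follow-up. The first hypothesis in the Discussion expects both training groups to improve relative to the control group.

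**The concern.** The comparison that was sized is a simple difference between two groups at week 16. The analysis is written around three visits that include the pre-treatment one. In a group-by-time analysis of variance, group enters either as an interaction with time, which is a contrast of changes, or as a main effect averaged over visits, including the visit before any training. Neither is the comparison that was sized.

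Change scores carry the noise of two measurements. When the correlation between visits is below 0.5, a change score is more variable than the post-test score alone, so the 80% stated for the outcome that sets the sample size would not be the power of the test that is run. The strongest predictor likely to be available, the participant's own baseline score, is collected but is not among the named covariates. With about 30 per group, chance baseline differences are then either ignored (post-test only) or over-corrected (change).

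**Working it through.** **Inputs (Sample size section).** Choice Reaction Time: between-group difference 118.8 ms, SD 160, n = 29 per group; within-group change 184 ms, SD 198, n = 12. Digit Span: between-group 2 items, SD 2.2, n = 20; within-group 1 item, SD 1.1, n = 12. Two-sided alpha 0.05. Power is from the noncentral t distribution unless marked z.

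**1. The plan's own figures reproduce.**
- Between groups, Choice Reaction Time: d = 118.8/160 = 0.7425. The normal formula gives n = 29 (power 80.7%, z); by t, power at 29 is 79.3%.
- Within group: a paired t-test on 184/198, and on 1/1.1, first reaches 80% at n = 12, as stated.
- Digit Span between groups: 2/2.2 at n = 20 gives 80.0%.
- Attrition: 29/0.9 = 32.2, rounded up to 33.

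**2. What the n of 12 says about the SD of change.** A paired t-test on 184 ms first reaches 80% at n = 12 only when the SD of change is about 197 to 207 ms. If 198 were instead a single-visit SD with correlation 0.5, the SD of change would be 198 × √(2 × (1 − 0.5)) = 198, the same value.

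**3. Group comparison on change, n = 29 per group.** d = 118.8/198 = 0.600; power 61.2% (62.7%, z). Over change SDs of 197 to 207 the power is 62% to 57%. Reaching 80% would take 45 per group (44, z). With all 33 per group retained it is 67%. This step needs no correlation.

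**4. Baseline-adjusted week-16 comparison.** With SD 160 at both visits:
- r = 1 − 198²/(2 × 160²) = 1 − 39204/51200 = 0.234
- residual SD = 160 × √(1 − 0.234²) = 155.5
- power at 29 per group = 81.5% (82.9%, z)

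If the SDs at the two visits differ, r = (SD₀² + 160² − 198²)/(2 × SD₀ × 160), where SD₀ is the baseline SD. SD₀ = 198 gives r = 0.40 and 86%. Over SD₀ from 130 to 220 the adjusted power is 80% to 89%.

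**5. Range over the unstated correlation.** SD 160 at both visits, n = 29, difference 118.8 ms. SD of change = 160 × √(2(1 − r)); residual SD = 160 × √(1 − r²). Post-test only is 79% in every row.

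| r | Change | Baseline-adjusted |
|---|---|---|
| 0 | 50% | 79% |
| 0.234 | 61% | 82% |
| 0.3 | 65% | 83% |
| 0.5 | 79% | 89% |
| 0.7 | 95% | 97% |

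**6. Digit Span at its own 2-item effect.** By the same formula r = 1 − 1.1²/(2 × 2.2²) = 0.875. At n = 20, post-test only has 80%; change and baseline-adjusted both exceed 99.9%. At n = 29, post-test only has 92.5%.

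**The case against.** A reader might infer that the plan commits itself to testing change and that the stated 80% is therefore wrong. The documents do not support that. The Analyses section lists differences between groups alongside changes over time and fixes no contrast, and for the post-test comparison that the Sample size section names, 80% is correct (79.3% by t, 80.7% by z). The change reading is the natural one, given the three visits and the hypothesis wording, but it is a reading.

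The correlation of 0.23 combines two SDs that may come from different studies and assumes equal variance at both visits. The Choice Reaction Time task was built for this project, so its own correlation is unknown. At r = 0.5 change loses nothing against post-test only, and at r = 0.7 it gains. This stands and is why the range has to be shown. A related argument, that 198 might be a single-visit SD, does not remove the 61%: the n of 12 holds the SD of change near 198 either way.

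It can also be said that the change SD should be paired with the change effect beside it: 184/198 at 29 per group, with a stable control group, gives 93.5%. But 184 ms is a within-group change. The between-group difference that the plan sets out to detect is 118.8 ms, and under randomization the expected difference in change equals the expected difference at post-test.

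It would be tempting to add that a raw post-test analysis leaves Digit Span badly underpowered. That needs a 1-item difference between groups, whereas the plan gives 1 item only as a within-group change; its between-group effect is 2 items.

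Finally, a journal article may leave model terms to a fuller document, and a group-by-time analysis is valid in a randomized trial. Both are true. The point is not a missing detail: the article states a sizing comparison, an analysis frame and a covariate list, and these do not match.

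**Conclusion.** The mismatch is real; its cost is conditional. If groups are compared on baseline-to-week-16 change and the SD of change is about 198 ms, Choice Reaction Time power at 29 per group is about 61% for 118.8 ms. A baseline-adjusted comparison has about 82%, assuming SD 160 at both visits and hence r = 0.23. Against the post-test comparison that was actually sized, the gain from adjustment at that correlation is modest, from 79% to 82%.

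The shortfall for change disappears at r of about 0.5 or above. Baseline adjustment is at least as powerful as either alternative over the whole range, so the recommendation does not depend on which correlation is true. Digit Span at its 2-item effect is not underpowered by any of the three methods. The 61% is for a pairwise baseline-to-week-16 contrast and should not be read as the power of an omnibus test over three visits. This is an improvement that should be made; it does not show that the planned analysis is invalid.

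**What to change.** In the Analyses section, make the between-group test an analysis of covariance of the week-16 score on group, with that test's own baseline score as covariate, plus age, education and gender. Name the three pairwise contrasts: exercise-only against control, combined against control, and combined against exercise-only. Analyse week 40 the same way and keep the analysis of variance over the three visits as a description of the time course.

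In the Sample size section, state the power for that model together with the correlation assumed: for example about 82% at 29 per group for 118.8 ms with SD 160 and r = 0.23, and 79% to 97% as r goes from 0 to 0.7.

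The cost is wording. Baseline scores are already collected for these measures, and no extra participants or visits are needed.

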## Discussion

"Nothing could be of greater importance to the imperatives imposed by global aging" than research into the benefits of exercise for cognition, according to Bortz [74]. This randomized controlled trial is designed to examine the effects of exercise training and combined exercise *and *cognitive training on the cognitive and physical functioning of community-dwelling older adults. It is hypothesized that

(1) both training groups will show significant improvements on measures of cognitive and physical functioning, relative to the control group,

(2) the combined training group (exercise *and *cognitive training) will show greater cognitive improvements than the exercise-only training group,

(3) improvements in cognitive functioning will be associated with improvements in aerobic capacity,

(4) improvements in cognitive functioning will be associated with improvements in psychological well-being; and

(5) participants will report positive experiences and outcomes from the two training programs.

If the training programs detailed in this protocol provide cognitive and physical benefits and are acceptable to older adults, they may represent a viable approach to improving cognitive functioning and quality of life in older adults. It is hoped that the findings from this study will add to a rapidly growing body of evidence which suggests that these types of interventions may be important for older adults, especially in a society that is facing the economic and social ramifications of an aging population.

## Abbreviations

GP: general practitioner; TICS: Telephone Interview of Cognitive Status; HRR: Heart rate reserve; ACSM: American College of Sports Medicine; RPE: Rate of Perceived Exertion; CLVT: California Verbal Learning Test; COAST: California Older Adults Stroop Test; D-KEFS: Delis-Kaplan Executive Function Scale; WMS: Wechsler Memory Scale; WAIS: Wechsler Adult Intelligence Scale; SDMT: Symbol Digit Modalities Test; TIADL: Timed Instrumental Activities of Daily Living; cm: centimeters; kg: kilograms; mm Hg: millimeters of mercury; bpm: beats per minute; SMWT: Six Minute Walk Test; kp: kiloponds; MAC-Q: Memory Complaint Questionnaire; SF-36: Medical Outcomes Study Short Form; GADS: Geriatric Anxiety and Depression Scale; HRHS: Health-related Hardiness Scale
